### Data analysis

#### Feasibility

Health professional and participant interviews and a technical assistance log will be independently coded using Framework analysis [51] based on CFIR domains and subsequently discussed by the two coders. This analysis will determine the acceptability and practicality of the Responsive CARE intervention and identify key contextual factors that impacted upon implementation. A third coder will be consulted if required to achieve consensus. From this, a network of core themes and sub-themes will be developed, informed by the CFIR constructs to guide evaluation of the factors that influenced implementation. Results from audits of ilearn digital metrics will inform assessment of demand and response to implementation strategies [52]. The descriptive data from the technical assistance logs will be analysed at project completion to quantify the number and type of issues experienced in implementation and the modifications (planned or unplanned) to the implementation blueprint. This data will be compared with ilearn digital records (of demand) to determine the overall feasibility of the Responsive CARE intervention in the burns outpatient clinic.

#### Patient-centred outcomes

Sociodemographic, clinical and intervention data will be summarised using descriptive statistics (e.g. mean and standard deviation and 95% confidence intervals) and presented for each group separately. Potential confounding variables for the outcomes are considered a priori to be the following: days to re-epithelialisation, percentage maximum burn depth, days post-burn at baseline, type of injury and number of surgical procedures (e.g. skin grafting) and severity of scarring and child traumatic stress symptoms. Potential confounding variables that are identified as significantly different or different to a clinically meaningful extent between the control and intervention group will be controlled for in analyses where appropriate. As this is a feasibility study, the study will likely be underpowered; therefore, quantitative outcomes will be interpreted only as preliminary findings.

Control period participants will be matched with intervention period participants on factors including age, gender, education and total body surface area burned to examine between group differences. Differences in outcomes between the groups will be analysed using generalised linear (mixed) models or equivalent analyses to examine differences at 3-month and 6-months post-procedure or 3-months and 6-months post-burn where applicable, adjusting for the baseline value of the outcomes where appropriate (with terms included for stratification and confounding variables where applicable). A sensitivity analysis will be conducted using imputation techniques to replace non-ignorable data that is considered to be missing at random over the follow-up period, to determine whether bias is likely in the complete case analysis.

Patient-centred outcome data will be stratified by age to coincide with different versions of patient-reported outcome measures for different age groups and caregiver report versus child report.

The mean difference in change scores for health professional’s knowledge and self-efficacy will be calculated for individual questions and analysed using a Wilcoxon paired test (assuming parametric assumptions are not likely to be observable in this relatively small sample).

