The acceptability of the Responsive CARE intervention to health professionalsThe demand for trauma-informed care training and use (or intended use) of the Responsive CARE intervention by health professionals in a tertiary, outpatient burn clinical settingTo what extent the Responsive CARE intervention training can be delivered using existing resources and infrastructure within the tertiary, clinical settingBarriers and enablers in the implementation environment and feasibility of the recruitment pathway to inform the amount and type of resources at different organizational levels (e.g. clinician, supervisor, manager) required to implement the intervention successfully

Specific objectives for the investigation of patient-centred outcomes are to:
Determine preliminary evidence of effectiveness of the intervention on a health professional’s knowledge, attitude and behaviours. This will provide preliminary indication of the extent to which skills and knowledge following the completion of the intervention have been applied and an evaluation of factors that drive clinician behaviour change.Determine preliminary evidence of effectiveness of the intervention on child’s acute pain, itch, distress (i.e. traumatic stress reactions), caregiver’s treatment satisfaction and health-related quality of life. This will provide an indication of whether the intervention can show change within this group. It is hypothesised that child participants will experience less acute pain, itch and distress in the posttest compared to the pretest period, and caregiver participants will experience enhanced treatment satisfaction in the posttest compared to the pretest, following staff completion of the responsive CARE intervention.Estimate healthcare resource use and costs of delivering the intervention to inform cost-related modelling for use in future economic evaluations of web-based education platforms.

The TIDierR checklist [35] and CONSORT-EHEALTH checklist (V.1.6.1) [36] have been used to detail the intervention and evaluation and CONSORT extension to pilot and feasibility trials [37] for reporting the study protocol.

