### Primary patient-centred outcomes

The primary outcome measures of effectiveness to be tested for the main study are pain (self-report or behavioural observation), itch and distress. The Face, Legs, Arms, Cry, Consolability (FLACC) pain scale [39, 40] will be completed by health professionals as a behavioural measure of pain severity. An 11-point numeric rating scale (NRS) will be used by parents and children 8 years or older to rate pain and itch intensity [41]. The NRS is scored from zero to ten, with zero equal to “no pain or itch” and ten equal to “unbearable pain or itch”. Distress will be measured using the Paediatric Emotional Distress Scale—Early Screener [40, 42] for children below 6 years and the Child Traumatic Stress Questionnaire [43] for children aged 7 years and above.

Patient-centred outcome measures to be collected at baseline, 3-months and 6-months post-baseline are summarised in Table 2.

**Table 2 Tab2:** Patient-centred outcome measures and timepoints when administered

Area of focus	Completed by			Outcome measure	Study period (control and intervention)		
	HP	C	YP		Baseline	3-months	6-months
Pain and itch (primary outcome)	X			The Face, Legs, Arms, Cry, Consolability (FLACC) [39, 40]	X	X	
		X	X	Numeric Rating Scale [41]	X	X	
Distress (primary outcome)		X		Pediatric Emotional Distress Scale – Early Screener^a^ [42]	X	X	X
			X	Child Traumatic Stress Questionnaire^b^ [43]	X	X	X
Stress		X		Perceived Stress Scale [44]	X	X	X
Satisfaction with treatment		X	X	Numeric Rating Scale (0 to 10)	X	X	X
Health-related quality of life		X	X	Brisbane Burn Scar Impact Profile [45–47]		X	X
		X	X	EuroQol-5D-Y^c^ [48, 49]	X	X	X
		X	X	CHU-9D^d^ [49, 50]	X	X	X

*HP* health professional, *C* caregiver, *YP* young person aged over 8 years (unless otherwise indicated)

^a^ For children below 6 years

^b^ For children aged 7 years and older ^c^ Administered to caregivers of children 3 years and older  ^d^Administered to caregivers of children 2 years and older

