### Primary health professional outcomes

Change in knowledge scores and self-efficacy will be measured using questions designed for the study and recorded as part of the online package (see Additional File 1 and 2).

Secondary and healthcare resource outcomes to be collected at baseline and 3-months post-baseline in the control and intervention period are as follows:
Administered pain relief: the number (percentage) of patients administered first and second line medications will be recorded. The dose of pain relief and other medication for symptom management will also be recorded.Rate and adjunct interventions (e.g. music therapy, counselling) for pain relief or reduction of stress symptoms.Number of psychosocial or mental health referrals: this will be recorded from medical records.Patient attendance rates at booked appointments and patient reminders: the percentage of booked appointments attended will be measured as well as the number of patient reminders sent by text, mail or phone as per standard practice.Time to wound healing: this will be measured using the time taken in days from the burn injury to ≥ 95% of the wound area re-epithelialized with no further wound dressings required. Re-epithelialization will be assessed by experienced burn consultant or specialised burn nursing staff.

In addition, hospitalisation-related resource use and costs will be collected from hospital administrative records for 12-months prior to the control period for each patient and for the 6-months after the intervention period for each patient for informing cost-related modelling for use in future economic evaluations of web-based education platforms.

Sociodemographic and clinical data will be collected from the following:

(1) The Queensland Paediatric Burns Registry or medical records (maintained by the Centre for Children’s Burns and Trauma Research) including percent total body surface area (TBSA), percent full thickness burn, length of time post-burn, spontaneous skin healing versus grafted site, type of burn and length of time to re-epithelialisation.

(2) Patient and/or caregiver self-report using a standard sociodemographics and clinical data form and questionnaires collecting data on household education, employment, income and occupation, scar location, skin type, age, gender and comorbidities

(3) Fidelity of the intervention based on the commencement and completion rate

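### The advance confounder list contains a primary outcome, a secondary outcome and variables that can arise after exposure, so a real benefit can trigger adjustment that shrinks the estimated effect

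*Protocol article*

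**What the plan says.** In the Protocol article, Data analysis, Patient-centred outcomes:

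- The confounder list opens with "Potential confounding variables for the outcomes are considered a priori to be the following: days to re-epithelialisation". It continues with maximum burn depth, days post-burn at baseline and type of injury, and closes with "number of surgical procedures (e.g. skin grafting) and severity of scarring and child traumatic stress symptoms". Only days post-burn is tied to a time point.
- The trigger for adjustment is a between-period difference: "Potential confounding variables that are identified as significantly different or different to a clinically meaningful extent between the control and intervention group" are to be controlled for, subject to appropriateness.
- The same subsection plans matching on factors including age, gender, education and TBSA. It handles baseline values of the outcomes in a separate provision, and it calls the quantitative results preliminary.

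Elsewhere in the article:

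- Primary patient-centred outcomes: "The primary outcome measures of effectiveness to be tested for the main study are pain (self-report or behavioural observation), itch and distress". One of the two distress instruments is "the Child Traumatic Stress Questionnaire [43] for children aged 7 years and above". The objectives at the end of the Background gloss the construct as "distress (i.e. traumatic stress reactions").
- Secondary outcomes, listed under Primary health professional outcomes: "Time to wound healing: this will be measured using the time taken in days from the burn injury". The end point is at least 95% re-epithelialisation with dressings no longer needed. The last sentence of that section allows other outcomes to enter analyses as predictors or confounders.
- Study design: the staff training month falls between the two periods, and baseline data are collected within each period.

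**The concern.** A confounder has to be settled before exposure. Two of the listed variables are, by the article's own definitions, outcomes of the study. Number of procedures and scar severity can also accrue after exposure, and nothing restricts them to earlier values.

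The selection rule makes this worse. The hypothesis is that distress will be lower in the intervention period. If that happens, the two periods differ on traumatic stress symptoms, and that difference is the condition for controlling for them. Pain and itch models would then be conditioned on something the training is meant to change. The Background itself links PTSD with more pain, and early pain treatment with lower PTSD severity, so a non-zero pain-distress correlation is plausible.

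For the genuine confounders on the list, the same rule can fail in the other direction. Whether burn depth or type of injury enters the model depends on a significance test in a modest sample, or on a judgement of clinical meaning with no stated threshold. At stake is the preliminary effect estimate that is meant to guide adaptation of the intervention.

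**Working it through.** **Inputs from the article.** Under Recruitment, 30 new referrals per month over two 3-month periods gives 30 × 6 = 180 children, which reproduces the stated figure. An equal split gives 90 per period. Age-specific instruments, and any children lost in matching, would make some comparisons smaller.

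**Assumptions.** The article gives no effect sizes, SDs, correlations or significance level. I use unit SDs, two-sided 0.05, covariate effects of 0.2 to 0.8 SD, and within-period covariate-outcome correlations r of 0.3, 0.5 and 0.7.

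**1. Which listed variables can follow exposure?**
- *Traumatic stress symptoms*: a primary outcome at baseline, 3 and 6 months. Training precedes the intervention-period baseline, so even that group's baseline value may reflect trained staff.
- *Days to re-epithelialisation*: healing requires that dressings are no longer needed, so a child enrolled at a dressing change has not yet reached it.
- *Surgical procedures and scar severity*: no time point. The only scar-specific instrument in Table 2 is taken at 3 and 6 months, not at baseline.
- *Burn depth, type of injury, days post-burn at baseline*: not affected by the training.

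**2. Attenuation.** In a linear model of the outcome on period and covariate, the period coefficient is

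adjusted effect = d(outcome) − r × d(covariate).

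| d(outcome) | d(covariate) | r | adjusted effect | loss |
|---|---|---|---|---|
| 0.50 | 0.50 | 0.3 | 0.50 − 0.15 = 0.35 | 30% |
| 0.50 | 0.50 | 0.5 | 0.50 − 0.25 = 0.25 | 50% |
| 0.50 | 0.50 | 0.7 | 0.50 − 0.35 = 0.15 | 70% |
| 0.50 | 0.20 | 0.5 | 0.50 − 0.10 = 0.40 | 20% |
| 0.50 | 0 | any | 0.50 | 0% |
| 0.25 | 0.50 | 0.5 | 0.25 − 0.25 = 0 | 100% (full mediation) |

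**3. How often does the significance limb fire on a real benefit?** With 90 per period, power ≈ Φ(d√45 − 1.96). For covariate effects of 0.2, 0.3, 0.5 and 0.8 SD this gives 0.27, 0.52, 0.92 and about 1.00. The larger the benefit, the likelier the adjustment. The clinical limb can only add to this.

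**4. The rule as a whole.** A simulation (6,000 replicates, 90 per period) adjusted only when the covariate differed at p < 0.05. With 0.50 SD on both variables, the mean estimates were 0.36, 0.26 and 0.16 SD at r = 0.3, 0.5 and 0.7. Power fell from about 0.92 without the covariate to 0.67, 0.48 and 0.29. Leaving the covariate out recovered the full 0.50 SD.

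**5. Genuine confounders.** The same formula at 0.25 SD gives Φ(0.25 × 6.708 − 1.96) = Φ(−0.28) = 0.39. At 0.30 SD it gives Φ(0.05) = 0.52.

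**The case against.** Several points on the other side have force.

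- *The rule is not purely a significance test.* An imbalance judged clinically meaningful also triggers adjustment, so 39% to 52% describes one limb only. That stands, though with no threshold the other limb cannot be assessed.
- *Matching is planned.* A reader might infer that case-mix differences are left uncorrected. The article does not support that: age, gender, education and TBSA are to be matched whatever the observed differences. Burn depth, type of injury and days post-burn are not named among the matching factors and rest on the rule.
- *Healing and surgery can predate enrolment.* Children attending for scar management are eligible and may have completed both, in which case these variables are legitimate severity markers. It would be wrong to call them always post-exposure. What is missing is the restriction to values complete before enrolment.
- *Distress adjusted for itself.* A reader might infer this. Nothing in the article plans to enter same-time distress in a distress model, and baseline outcome values have their own provision. The supportable worry is stress symptoms entering models of other outcomes.
- *Appropriateness and preliminary status.* The qualifier leaves discretion but excludes no outcome or later variable. Calling results preliminary acknowledges imprecision and lowers the stakes; it does not remove bias.

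No figure in the article shows that staff training changes healing time or number of procedures. If it does not, adjusting for them costs nothing through this route.

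**Conclusion.** The point holds as a moderate fault in the analysis plan. The list mixes a primary outcome, a secondary outcome and undated variables with genuine confounders, and the trigger makes adjustment likelier as the benefit grows.

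Under assumed equal 0.5 SD effects, the loss is 30% to 70% for r between 0.3 and 0.7. It is 20% if the covariate effect is only 0.2 SD with r = 0.5, and nil if training does not move the covariate. A reader might conclude that the plan adjusts the whole effect away. That is true only if the effect runs entirely through the covariate, and the article gives no figures to establish that. All magnitudes rest on assumed effects and correlations; only the 180 children come from the article.

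The severity is moderate because the article reads its quantitative results as preliminary and, under Limitations, declines to attribute outcomes to the intervention alone.

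**What to change.** 1. Remove child traumatic stress symptoms from the confounder list, along with any other variable not fixed before exposure. Allow healing time, surgery or scar severity only where complete before enrolment, for example in children enrolled for scar management, and state that time point.
2. Replace the difference-triggered rule with one fixed pre-exposure set in every between-period model, whatever the observed differences: burn depth, type of injury and days post-burn at baseline, plus the matching factors age, gender, TBSA and education.
3. Report any model containing post-exposure variables only as exploratory mediation.
4. Bring the sentence that lets other outcomes enter as predictors or confounders into line with this.

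The cost is a change of wording before analysis. The variables in the fixed set are already among the planned data, so no new data collection is needed.

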## Method

### Study design

The feasibility study will employ a pretest posttest observational design using mixed methods to evaluate acceptability, demand, implementation and practicality [34] of the Responsive CARE intervention. Using a mixed methods approach will allow for the collection of quantitative data in terms of the demand for the intervention as well as rich qualitative data to understand the factors affecting implementation that may ultimately impact on the intervention’s sustainability and/or scalability. Purposive sampling will be used for the qualitative study components. Interviews will cover five main areas: understanding of trauma-informed care practice, experience of trauma-informed care, clinician’s readiness to change, acceptability of the Responsive CARE intervention and identify potential barriers and enablers to implementing an e-learning package within organizational culture.

A mixed method, pretest posttest comparison design will be used to examine preliminary effectiveness, with consecutive sampling of children and caregivers. Baseline quantitative data will be collected during a 3-month control period followed by a 3-month intervention period. Follow-up of participants will be completed at 3 months and 6 months after baseline for participants in the control and intervention periods. Between the control and intervention periods, there will be a 1-month period to implement the e-learning intervention. Qualitative interview data will also be collected from caregivers in the control and intervention periods, who will be purposively sampled.

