### Study setting

The study will be conducted at the outpatient clinic for children with burns at a specialist publicly funded, teaching children’s hospital located in Brisbane, Australia. The clinic accepts referrals for all children and young people with burns (0–18 years) across the state of Queensland and Northern New South Wales and receives approximately 1300 new referrals per year. The burn clinic team is a multidisciplinary team comprised medical team (5 burn consultants and four teams of rotational registrars and residents), specialist burn nursing staff (1 burn clinical nurse consultant, 1 burn clinical nurse and up to 3 registered nurses), allied health staff (1–2 physiotherapists, dietitian, social worker, music therapist, consultant liaison mental health service and up to 6 occupational therapists), as well as up to 4 administration and 5 higher degree research staff. Core staff in attendance at each burn outpatient clinic include medical, nursing, allied health (allied health assistant, occupational therapy, physiotherapy, social work) and administrative staff. Burn specific experience ranges from < 1 month to over 30 years within the multidisciplinary team. There are generally up to 2 clinical trials or other research projects occurring within the recruiting centre at any time of the year. At the time of the study, the organizational approach towards educational or care strategies to reduce paediatric medical traumatic stress in burn outpatients was referral to psychosocial services (generally social work) and participation in a clinical trial (if aged below 6 years and screened at high risk for PTSD) that commenced at the beginning of this study [14].

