### Recruitment

#### Quantitative study component

The sample size will be based on children available to be recruited during the control and intervention period, which is anticipated to be 180 children (based on an average of 30 new referrals each month to the burn centre). It is anticipated up to 50 health professionals may be eligible to access the intervention, with an estimated 50% turnover of staff in the training and intervention period (as the recruiting centre is a teaching hospital). Health professionals that commence working at the recruiting centre during the intervention period will be informed about the study by a clinician researcher (MS) or research assistant and offered personal log-in details following informed consent.

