## Limitations

The use of a pretest posttest study design for feasibility testing of the intervention has limitations, in that pretest posttest studies do not have control over things that might be changing at the same time as the intervention, so outcomes cannot be attributed to the intervention alone [55]. However, in health services research, these study designs can be valuable to inform a more holistic, population-based, ecological systems science that attends to contextual factors and external validity [56].

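### Confounders named in advance are adjusted for only if the two periods are seen to differ, significantly or by a clinical judgement with no threshold, so the remaining bias depends on a choice made after seeing the data

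*Protocol article*

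**What the plan says.** The design is sequential (Study design): "Baseline quantitative data will be collected during a 3-month control period followed by a 3-month intervention period". The Limitations section accepts that "pretest posttest studies do not have control over things that might be changing at the same time as the intervention".

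Under Data analysis, Patient-centred outcomes, the list of a priori potential confounders begins "days to re-epithelialisation, percentage maximum burn depth, days post-burn at baseline, type of injury and number of surgical procedures (e.g. skin grafting" and goes on to scar severity and child traumatic stress symptoms. The next sentence sets the entry rule: variables "identified as significantly different or different to a clinically meaningful extent between the control and intervention group will be controlled for", where appropriate. Neither criterion is given a number. The same section says "As this is a feasibility study, the study will likely be underpowered" and that quantitative results will be read only as preliminary.

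Two other controls are planned there. Control children are to be "matched with intervention period participants on factors including age, gender, education and total body surface area burned", and models adjust for the baseline value of the outcome where appropriate.

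**The concern.** The periods are not randomised, so case mix can truly differ between them, and covariate adjustment is one of the few defences available. Naming confounders in advance is the right start, but the entry rule undoes much of it, because each variable must first show a difference in the data.

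A between-period p-value is a poor screen. Confounding depends on the size of the imbalance and on how strongly the variable predicts the outcome. The test ignores the second and tracks sample size. In a study that the article itself calls underpowered, a non-significant difference is not evidence of balance, and several modest shifts can each pass unflagged and add up.

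The clinically meaningful criterion could repair this. Without a threshold, though, it is a judgement made with the data in view, so the analyst in effect decides how much confounding stays in the estimate. Precision is also lost whenever a prognostic variable is left out.

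**Working it through.** **Inputs.** Total sample: "which is anticipated to be 180 children (based on an average of 30 new referrals each month to the burn centre" (Recruitment, Quantitative study component). Check: 30 × 6 months = 180, as stated. An equal split gives 90 per period; this is an assumption, since only the total is given. Also assumed: two-sided 5% for the significance criterion, and 0.1, 0.2 or 0.25 SD (standardised mean difference, SMD) as possible thresholds for the clinical criterion.

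**Chance that the significance criterion flags a true shift d (in SD).** The standard error of the difference is √(2/90) = 0.149 SD. The smallest observed difference reaching p<0.05 is 1.973 × 0.149 = 0.294 SD. Power is approximately Φ(d/0.149 − 1.960):

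| True shift (SD) | d/0.149 − 1.960 | Flagged |
|---|---|---|
| 0.2 | −0.62 | 27% |
| 0.3 | 0.05 | 52% |
| 0.4 | 0.72 | 77% |
| 0.5 | 1.39 | 92% |

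The 50% point is 1.960 × 0.149 = 0.29 SD. For a binary factor, 20% against 30% is flagged 34% of the time. If the screen were run within age strata, power would fall: with 45 per period a 0.3 SD shift is flagged 30% of the time, with 30 per period 21%.

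**Bias left in the period difference, three confounders.** Simulation with 90 v 90, no true effect, independent confounders each shifted 0.2 SD in the same direction, correlation r with the outcome, and no baseline-outcome term. With no adjustment at all the bias would be 3 × 0.2 × r = 0.18 SD (r = 0.3) or 0.24 SD (r = 0.4).

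| Rule | Bias (SD), r = 0.3 to 0.4 | False-positive rate |
|---|---|---|
| Significance only | 0.08 to 0.12 | 7 to 11% |
| Significance or SMD > 0.25 | 0.06 to 0.09 | 6 to 7% |
| Significance or SMD > 0.2 | 0.04 to 0.05 | under 5% |
| Significance or SMD > 0.1 | under 0.01 | about 4% |
| Always adjust | 0 | about 5% |

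The significance screen removes more bias than its 27% hit rate suggests, because it acts in the samples where the observed imbalance is largest. All three confounders enter the model together in about 0.27³ = 2% of samples on significance alone, and in about 5%, 13% and 46% at thresholds of 0.25, 0.2 and 0.1. At r = 0.4 the SD of the estimate is about 0.13 under the significance-only rule and about 0.11 with fixed adjustment.

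**One confounder, shifted 0.2 SD, r = 0.3 and 0.5.** Bias is 0.027 and 0.047 SD on significance only, 0.018 and 0.034 SD at a threshold of 0.25, 0.010 and 0.019 SD at 0.2, and 0.002 SD or less at 0.1. The false-positive rate stays at 4.3 to 5.4% throughout.

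**Sensitivity to sample size.** Study setting says the clinic "receives approximately 1300 new referrals per year", which is 1300/12 = 108 a month or 650 in six months, against the 30 a month used for the sample size. At 325 per period the significance criterion would flag a 0.2 SD shift 72% of the time. The article does not reconcile the two figures; the results above follow the stated 180.

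**The case against.** A reader might infer that confounders are adjusted for only when significantly different. The text does not say that: a clinically meaningful difference triggers adjustment by itself, and at a threshold of 0.2 SD or less the error inflation disappears and the bias more than halves. The 7 to 11% error rate therefore describes a rule in which the second criterion never acts, and is not a property of the plan as written. Nor do real shifts in general go unadjusted: even on significance alone that is the usual result only below about 0.29 SD.

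Other controls count too. Matching covers age, gender, education and total body surface area, from an open list. If baseline outcomes are adjusted for (assumed residual correlation 0.5, confounders acting equally at both times), the significance-only bias in the three-confounder case falls to 0.033 to 0.036 SD, with 5.3 to 6.5% error. The close of the outcomes section also says, with no significance condition, that the clinical and sociodemographic data will enter analyses as predictors or confounders. Results are declared preliminary, and no confirmatory decision rests on these p-values.

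This narrows the size of the problem but does not remove it. The named matching factors do not include days post-burn, burn depth or injury type. Baseline adjustment is only where appropriate, and the Brisbane Burn Scar Impact Profile has no baseline measurement in Table 2. The general sentence on confounders does not override the specific rule in the analysis section. A final covariate list may well be left to an analysis plan, but the article states a selection rule, and that rule is what needs changing.

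**Conclusion.** The point holds as a fault in a stated rule: pre-named confounders enter the models only after a between-period comparison, with one criterion that is insensitive at about 90 per period and another that has no threshold. In the three-confounder setting the resulting bias runs from under 0.01 to about 0.12 SD, according to a choice not yet made. With one confounder it is at most about 0.05 SD. These figures rest on the equal split, the 5% level, same-direction shifts of 0.2 SD, the assumed correlations and no baseline-outcome term.

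A reader might also infer that every listed variable should simply be forced into the model. The documents do not support that: days to re-epithelialisation, surgical procedures and scar severity can arise after enrolment and may be affected by care. Severity is minor to moderate, given the declared preliminary status of the results.

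**What to change.** Replace the entry rule with a fixed set, for example: *Days post-burn at baseline, type of injury and burn depth (as assessed at or before baseline, where available) are included in every between-period model whatever their observed difference.*

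The qualifier on burn depth is needed because the article lists percentage maximum burn depth and percent full thickness burn without saying when either is assessed. Keep days to re-epithelialisation, surgical procedures and scar severity out of this set. Report baseline differences between periods as standardised differences, and do not use them to select covariates.

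The cost is one sentence and a few degrees of freedom. Time post-burn, type of burn and a burn-depth measure are already among the planned clinical data; only the timing of the depth assessment has to be settled.
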